## Abstract

**Background:**

In recent decades, parents have been involved in programs that aim to improve parenting style and reduce child behavior problems. Research of preventive parenting programs has shown that these interventions generally have a positive influence on both parents and children. However, to our knowledge there is a gap in the scientific literature when it comes to randomized controlled trials of brief, manual-based structured programs which address general parenting among the population, and focus on promoting health. A four-session universal health promotion parent group program named All Children in Focus was developed. It aims at promoting parental competence and children’s positive development with the parent–child relationship as the target. There is currently no randomized controlled trial existing of the program.

**Methods/Design:**

A prospective multicenter randomized wait-list controlled trial is being conducted. Approximately 600 parents with children ranging in age from 3–12 years have been recruited in eleven municipalities and city districts in the County of Stockholm, Sweden. Parents are randomized at baseline to an intervention group, which receives the program directly, or to a waiting-list control group, which participates in the program six months later. Changes in parenting and child health and development are assessed with measures immediately post-intervention and six months after the baseline. Observations of a minor group of parents and children are conducted to explore possible relations between parental reports and observed behaviors, as well as changes in the interaction between parent and child. Further, data collected within the evaluation will also be applied to evaluate the possible cost-effectiveness of the program.

**Discussion:**

This paper describes a study protocol of a randomized controlled trial. Except for the quantitative outcome measures to evaluate the effectiveness of All Children in Focus, this protocol also describes health economic and qualitative analyses to deepen the knowledge of the program. We further discuss some issues regarding the implementation of the program in municipalities and city districts.

**Trial registration:**

Current Controlled Trials ISRCTN70202532

## Background

Employment of various methods for supporting parents has been stressed as important to promote children’s health and development as well as to prevent different health problems. The support to parents can be delivered as programs or policies [1]. A common strategy or approach that has been deployed in recent decades is to involve parents in programs that aim at improving parenting style. Most of the research covering parental support programs focuses on established parental or child risk factors that could contribute to avoiding health or developmental problems for children rather than promoting health and development [2]. To prevent such negative outcome and to counterbalance risk factors, many programs aim for strengthening or developing protective factors [1-3]. Preventive programs such as the Incredible Years [4], COPE [5] and Triple P [6] were developed in a non-European context in the 1980s and 1990s.

Research of preventive parenting programs has shown that these interventions generally have a positive influence; first on children, by treating a variety of child behavior problems [7-12], and second, on parents, by improving parental behavior and skills [7,11,12]. Nevertheless, most of these interventions seem to address children’s or adolescents’ ill-health and disruptive or problem behavior, and tutor parents in methods and techniques for preventing or dealing with their children’s problematic behaviors [13-15]. However, studies of support for parents through health promotions of children’s mental development and well-being seem, to our knowledge, to be limited in the scientific literature when it comes to general parenting among the population [16,17]. This may indicate a shortage of development and research on interventions influenced by a salutogenic perspective, and that address the universal level of parenting. Such an intervention could strive for empowering parents in their general comprehension of confidence and capacity, and to strengthen their self-efficacy.

Parental empowerment in terms of formulating their own goals for what aspects they want to strengthen in their relationships with their children has been suggested as a topic for universal parental programs [18]. Encouraging parents to decide for themselves about what to emphasize in the upbringing of their children could, besides as an expression of empowerment, also be viewed as a tool to strengthen parental competence and parental self-efficacy [19]. In evaluations of parenting interventions, it is also valuable to study whether there are families that benefit more or less from interventions, as well as if there are variables mediating the outcome. Earlier research has investigated effects of moderators and mediators on outcome, where different factors such as family demographics (e.g., socioeconomic status), participation (e.g., attendance level), child variables (e.g., age, gender), and parent variables (e.g., mental health, positive parenting), have been shown to affect the outcome [12,20]. Since mediating and moderating factors mainly seem to be evaluated concerning prevention programs, it is also vital to investigate the potential effects of these in a universal health promotion program. Moreover, there is a lack of solid health economic evaluations of parent interventions, especially of universal interventions aiming at promoting mental health [21,22]. Since societal resources are scarce, priorities must be made. By identifying costs, savings, and consequences for health and well-being, it could be examined whether investments in universal parenting interventions are a wise way of utilizing resources compared to other health initiatives.

The program in this trial, All Children in Focus, later referred to as the ABC-program as well (in Swedish - Alla Barn i Centrum), consists of structured, universal health-promotion group meetings that target parents of children aged 3–12 years. The purpose of the program is to strengthen the relationship between parents and their children. The ABC was developed from 2009 to 2011, and has been piloted during its development in twelve municipalities and city districts in the County of Stockholm, Sweden.

### Aims

The main objective of our study is to evaluate the effects of a universal parenting program, the ABC-program, through promotion of parental self-efficacy as well as children’s development and well-being. The following research questions are investigated:

1) What effects does participation in the ABC-program have on parental skills, self-efficacy, and children’s health immediately after, and 6 months post baseline?

2) Do program fidelity and delivery by group leaders mediate the outcome of the program?

3) Are either parental level of attendance at sessions or use of program components related to effects of the program immediately, 6, and 12 months post baseline?

4) Does impact of the program differ depending on the child’s gender, age, parental ethnicity, education, income, or mental health?

5) Does parental improvement in emotion regulation or self-efficacy mediate change in children’s health and development?

6) Is the ABC-program cost-effective?

7) Is self-rated parental competence related to observed parent and child behaviors?

8) Are there changes in the interaction between parent and child?

## Methods/Design

The ABC-program is evaluated in a prospective, multicenter, randomized wait-list controlled trial (RCT), in a ratio of 1:1, to be allocated to the intervention group or a waiting-list control group. The RCT was undertaken after a first-time pilot study from 2009–2011 where 405 parents were recruited, after which the ABC-program and questionnaires included were slightly modified. Parents with children 3–12 years old in the municipalities and city districts taking part in the RCT-study will be asked to participate further, from 2012–2014. Those who accept participation after receiving verbal information and providing written informed consent, will be randomized to receive the ABC-program either directly or after six months (on a waiting-list). Parents randomized to a delayed-onset ABC-program starting after 6 months compose the control group. There will be approximately 300 parents each in the intervention and control group, respectively. Follow-ups are employed 6 and 12 months after baseline (See Figure 1).

**Figure 1 F1:**
[figure not shown]
Timeline detailing the research procedure for the ABC-RCT.

### Setting

Parents with children ages 3–12 years were recruited in eleven municipalities and city districts in the County of Stockholm, Sweden. The participating municipalities and city districts represent a geographical coverage of different parts of the county, including different groups of parents regarding education, income, and ethnicity. The ABC-program is performed with trained personnel/ABC-group leaders at local agencies, such as preschools, schools, and family health centers.

### Participants, recruitment and randomization

Information about the study has been distributed through advertisements in local papers, supermarkets, child health centers, family centers, preschools, schools, as well as the websites of the participating municipalities and city districts. Joint materials such as posters and leaflets were available for use with recruitment efforts. The most common recruitment strategies were through personal contact with parents, information at schools and preschools, websites, advertisements, and a specially produced ABC promotion video. The video was shown in connection with the checkouts at grocery stores. Other strategies entailed letters to parents and contacts with maternity health services and child health services. Some local differences occurred; that is, a few of municipalities/city districts recruited in a more limited way, while most others recruited more comprehensively. Interested parents were invited to local information meetings at local premises such as schools and municipal buildings in February-March 2012 (Wave 1), and September-October 2012 (Wave 2). Meetings were held in the evenings, and parents were offered some beverages and snacks. The researchers have given information about the RCT-study, and group leaders or contact persons have explained about the content of the ABC-program at the information meetings. Parents were also informed about participation being voluntary, and that they could withdraw at any time without having to state a reason. Parents were also given printed information together with a consent form to be signed if they agreed to participate in the trial. The signed consent forms were collected, and afterwards baseline measures (via questionnaires) were taken. For parents not attending the meeting, information, consent, and baseline measure questionnaires were sent home with a pre-stamped envelope to be returned to the researchers. In Wave 1, 311 parents joined the study and in Wave 2, 310 parents joined.

Randomization to allocate parents to intervention or control groups was performed after collection of baseline data (See Figure 2). In families where both parents announced interest to participate, both were invited to participate, but data will be pooled if their answers in the questionnaires cover the same child. Randomization was conducted at the level of individual parents for each municipality/city district: a 1:1 ratio, using SPSS version 20. However, couples were randomized together as one unit.

**Figure 2 F2:**
[figure not shown]
The ABC-RCT CONSORT flow diagram.

Parents participating in the trial received incentives during and after the trial. After completion of the first follow-up questionnaire, parents received entrance for the whole family to an open-air museum located in the city of Stockholm. About the same time, parents in the control group received a chocolate bar (parents in the first wave) and reflectors (parents in the second wave). When the final follow-up questionnaire has been conducted, 12 months after the baseline, parents will receive a gift card offering them either a paperback book or three movie rentals.

#### Recruitment of contact persons

Initially, one contact person was recruited from each municipality and city district to coordinate and to serve as a link between research and municipalities/city districts. Their tasks were to recruit group leaders and parents to the trial, as well as, to provide premises for information meetings and for ABC-groups.

#### Recruitment and training of group leaders

Most of the group leaders were recruited from each municipality/city district. In total 67 group leaders were recruited. Twenty seven of them received training during the pilot study of ABC, while 40 were trained during the RCT. By profession they were, for example, preschool teachers, social workers, and pedagogues.

During the trial, trainings were held for new group leaders, and led by ABC instructors; the other group leaders were trained by the developers (the method group described below) of ABC during the pilot study. Group-leader training lasted four and a half days, followed by continuous follow-up tutoring.

All group leaders were informed about the trial; new group leaders at their first training session and old group leaders were invited to meetings held by the researchers. Group leaders gave their written consent to participation in the trial, confirming that they were informed about the four tasks that they were obligated to participate in:

1. Video recording of one of the four sessions (this session was randomized by the researchers).

2. Filling in a group-leader checklist after each session. (The checklist comprised questions regarding how the session was performed).

3. Filling in an attendance list for parents participating in the sessions.

4. Delivering questionnaires to parents regarding their commitment to the method at the beginning of sessions two, three, and four.

#### Basic skills for group leaders

Each group is run by two group leaders, important skills for group leaders during the ABC sessions are to encourage and empower the parents, activate the discussion in the group, and structure the discussion to the topic. The skills are further illustrated in Table 1.

**Table 1 T1:** Description of required basic skills for group leader

**Group leader skill**	**Purpose**	**Examples and methods**
**Validate**	Strengthen parents’ confidence in their own ability.	**Encourage** parents’ work with the ABC: "It sounds like you had a breakthrough moment with ABCD although the time was short, wonderful!"
	Be a model for the parents.	**Treat parents emphatically**: "It sounds like you’ve had a rough week, no wonder you feel tired."
	Create a permissive atmosphere so that parents dare raise difficulties.	**Encourage** parents’ responses and contributions.
**Activate**	Increase participation.	**Return questions**:
	Maintain the interest of the parents.	1. What are your thoughts about this?
		2. Does anybody else have any comments?
	Encourage activity of the parents when this is desirable.	Wait for the parents’ response. Give them time to think of discussion questions.
	Ensure that everyone gets the same opportunity to talk	Let the parents discuss in small groups.
**Structure**	Increase clarity.	**Start and end** the meeting on time.
	Stick to the content of the material and bring the discussion back to the theme.	**Write the agenda** on the board or flip chart.
		Go through the hits according to **group leader material**.
		**Cancel discussions that drift from the subject** and return to contents by thanking for the comments, summarizing and moving on.
		Talk in **behavioral terms**: “What does Karin *do* when she is angry?”, “What do you *do*?”

#### Group leader skills and fidelity

In order to study facilitator skills and fidelity to the ABC-program for group leaders, each pair of group leaders is video recorded. Before starting the group, randomization is made of which session of the total four is going to be recorded (with parental approval). Only the two group leaders are recorded visually on the video, while only the voices of participating parents are recorded; parental approval of the recordings has to be collected.

#### Drop out before intervention

During the first recruitment wave, 37 parents came to information meetings or got information sent home about the trial, but chose not to participate. On the second wave, there were 54 parents who did not want to participate in the trial after having received information. The most common reasons for not wanting to participate were time constraints, language barriers, and parents being indisposed to dates when the ABC-groups were to be held. A few parents were not interested in participating in research, while some parents did not state a reason for not wanting to participate. Very few parents declined participation because of the randomization procedure, which had made it uncertain whether they would be assigned to the same ABC-group as a friend, or because they wanted some other kind of support (e.g., individual support). Some parents also brought information home to their partners or to friends who they thought might also be interested in participating in the trial. A majority of these were interested and chose to participate. It should be noted that child care concerns were a barrier for some partner participation.

### Power and sample size

The intention has been to include 300 families in the intervention and control groups respectively. According to a sample size calculation, 107 parents are needed in each group to allow a detection of an effect size of 0.4 at 90% power and the p < 0.05 level of significance, with a one-tailed test. It is also of importance to take into account the effects of a cluster design, as the intervention is offered to groups while effects of this have to be identified in intra-class correlations (ICC) [23]. The design effects of this in a universal promotion parenting program are not identified earlier, while an estimate of 0.01 could be considered as conservative. This would require a sample of 220 parents in each group [23].

Families that do not fulfill participation in the ABC will also be followed together with families attending the intervention. An attrition rate of at least 20% is expected at the 6-month follow-up after baseline, in accordance with results from somewhat similar studies [24,25]; this is why an over-recruitment will be done.

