### Intervention

ABC targets one of the most important protective factors for children – the parent–child relationship. The theoretical base is social learning theory [26], with focus on how children learn from their parents and how parent behavior can promote a positive relationship. Moreover, attachment theory [27] is included in relation to child-directed play to enhance parental attunement to the child. Influence of the external environment on family functioning has been incorporated by addressing parental stress and circumstances outside the family [28,29]. ABC consists of components included in parental programs demonstrated to be effective [11,30]. Also considered, were unpublished interviews with parents about content and factors that could contribute to participation in a program, as well as interviews with potential group-leaders. Moreover, a pilot study was performed with parents in order to test the feasibility of the components.

In this study, these components are being tested with a universal approach. ABC consists of four 2.5 hour structured sessions with approximately 10 parents in each group. The sessions are held every other week with homework between the sessions. After the six-month follow-up, a booster session is offered to the parents. The themes of the four sessions are: Showing love, Being there, Showing the way, and Pick your battles. In the first session, the parents set goals that are followed-up at the last session. Short films and role plays are used to facilitate discussions in the group. Each parent receives a copy of a binder with the content of the sessions with room to take notes. In the following section, the content of the four sessions are summarized.

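### The 220 parents per group does not follow from an ICC of 0.01 with groups of about 10, which gives about 117; the cluster size and formula need to be stated

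*Protocol article*

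**What the plan says.** Under Power and sample size, the protocol article first gives a figure without clustering: "107 parents are needed in each group to allow a detection of an effect size of 0.4 at 90% power", at "the p < 0.05 level of significance, with a one-tailed test". It then says that clustering has to be allowed for because the program is delivered in groups. On what is known about the size of this effect it says: "The design effects of this in a universal promotion parenting program are not identified earlier". The conclusion follows directly: "an estimate of 0.01 could be considered as conservative. This would require a sample of 220 parents in each group".

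That section gives neither the number of parents per cluster nor the inflation formula. The Intervention section describes "structured sessions with approximately 10 parents in each group", which is the only program-group size in the article. Expected attrition of at least 20% at six months comes in the next paragraph of the sample-size section, as the reason for over-recruiting. It is therefore not part of the 220. The intention to include 300 families per arm is stated before any of the calculations.

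**The concern.** An ICC of 0.01 with small groups should raise the sample size only slightly, yet the stated requirement roughly doubles, from 107 to 220. This is the only sample-size figure in the article that allows for clustering, and it disagrees with the inputs printed around it. A reader cannot tell which input is wrong. The design might have been sized for an ICC of 0.01, or it might tolerate a much larger one. What is at stake is whether the stated justification under clustering can be checked. There is a second, smaller point: 0.01 is called conservative just after the text says that no earlier value is known.

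**Working it through.** **Inputs.** From Power and sample size: standardised effect 0.4, power 90%, one-tailed 0.05, 107 per group without clustering, 0.01 for clustering, 220 per group with clustering, attrition 20%. From Intervention: about 10 parents per group. The sentence grammatically attaches 0.01 to design effects. I read it as the ICC, because the preceding sentence is about ICCs and a design effect of 0.01 would make no sense as an inflation.

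**Step 1: reproduce the 107.** n = 2(z_0.95 + z_0.90)^2 / d^2 = 2(1.645 + 1.282)^2 / 0.4^2 = 107.05 per group. The stated figure reproduces.

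**Step 2: apply the stated clustering.** Design effect = 1 + (m - 1) x ICC = 1 + 9 x 0.01 = 1.09. Then 107 x 1.09 = 116.6, or 117 per group. The stated 220 is 220/116.6 = 1.89 times that.

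**Step 3: what 220 would need.** 220/107 = 2.056. There are two ways to reach that design effect from the printed 107:

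- ICC kept at 0.01: m = 1 + 1.056/0.01, about 107. With m = 107 exactly, 107 x (1 + 106 x 0.01) = 107 x 2.06 = 220.4.
- m kept at 10: ICC = 1.056/9, about 0.117.

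The first matches almost exactly and uses a number already in the calculation, the per-arm sample size. Neither a cluster of 107 parents nor an ICC of 0.117 is stated in the article.

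**Step 4: other routes.**

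| Variant, ICC 0.01 unless stated | Per group |
|---|---|
| m = 8 | 114.5 |
| m = 15 | 122.0 |
| m = 27.3 (300 per arm over 11 districts) | 135.1 |
| m = 54.5 (600 in all over 11 districts) | 164.2 |
| m = 10, then 20% attrition (116.6/0.8) | 145.8 |
| m = 10, two-sided base of 131.3 | 143.2 |
| m = 10, two-sided, then 20% attrition | 179.0 |
| m = 10, ICC 0.10 instead of 0.01 | 203.3 |

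One can force 220 by changing more than one thing. A two-sided base needs m of about 69. Folding in 20% attrition needs m of about 65 on the one-sided base, or about 35 on the two-sided base. A two-sided test at 95% power with m = 10 and attrition gives 222. Each of these contradicts the stated test, the stated power or the place where attrition is introduced, or needs a cluster size that the article does not give.

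**Step 5: consequence for power.** With effective size n_e = n / design effect, one-sided power is Phi(0.4 x sqrt(n_e/2) - 1.645). At m = 10, both arms inflated:

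| Per group | ICC 0.01 | ICC 0.05 | ICC 0.10 |
|---|---|---|---|
| 117 | 90.1% | 81.5% | 71.7% |
| 220 | 99.1% | 96.7% | 91.9% |
| 240 (300 less 20%) | 99.5% | 97.7% | 93.7% |

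**The case against.** The strongest defence is that the sample-size section states no cluster size and credits 220 to a cited source that is not available here. The 117 therefore takes its cluster size from the description of the intervention, and a journal article may leave formula and inputs to a fuller document. Part of this stands: the 117 depends on reading the program group as the cluster. But the section itself names delivery in groups as the source of clustering, and the article gives one size for those groups. Sizes of 8 to 15 move the answer only from 115 to 122. Condensation can explain a missing formula. It does not explain a printed result that disagrees with the printed inputs.

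Four stronger readings are tempting, and the document does not support them.

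- *The trial is underpowered.* The error runs the other way. At the stated effect size, test and ICC, 220 per group exceeds 90% power by a wide margin.
- *The ICC of 0.01 is wrong, or a slip for 0.1.* An ICC of 0.10 gives 203, not 220, while 0.01 gives 220.4 once the arm size is used as the cluster size. The likelier slip is the cluster size. Whether 0.01 is low for such a program needs outside data. What can be said is that a cautious ICC is a high one, and that the label conservative has no support in a text that reports no earlier value.
- *The target of 300 per arm rests on 220.* The article does not say so. Allowing 20% loss gives 220/0.8 = 275, so the link is only a guess.
- *Inflating both arms is a further error.* Wait-list parents attend no program group before the six-month comparison, so clustering could be modelled in one arm only. Inflating both arms of a 1:1 trial errs toward a larger sample and is an acceptable simplification.

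**Conclusion.** The point holds as an error of derivation and reporting, of minor to moderate weight. With an ICC of 0.01 and groups of about 10, the requirement is about 117 per group before attrition (146 after 20% loss), and the stated 220 is 1.89 times the unadjusted-for-attrition figure. This assumes that 0.01 is the ICC, that the cluster is the program group, that group sizes are roughly equal, and that both arms are inflated alike. Entry of the per-arm sample size as the cluster size is the most likely cause, inferred from the near-exact match; the article does not confirm it. On the same assumptions, 220 per group keeps 90% power up to an ICC of about 0.117, so the planned size is not put in doubt at the stated inputs.

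**What to change.** State the cluster size (about 10 parents) and the formula, design effect = 1 + (m - 1) x ICC. Then do one of two things:

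- replace 220 with about 117 per group for ICC 0.01, noting that both arms are inflated and that attrition is not yet included; or
- keep 220 and say that it retains 90% power up to an ICC of about 0.117 at group size 10, under the same both-arm inflation.

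If another cluster size was intended, state it and show how it gives 220. Give a source for calling 0.01 conservative, or remove the word.

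If the authors prefer to model clustering in the intervention arm only, both figures must be recomputed together. The requirement becomes 107 x (1 + 1.09)/2, about 112 per group. For 220, the intervention-arm design effect would be 2 x 2.056 - 1 = 3.11, so the tolerated ICC is 2.11/9, about 0.235. The one-arm and both-arm figures should not be mixed.

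The cost is a few words and one recalculation. Recruitment is unaffected: 311 + 310 = 621 parents have already joined.
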